**7.4. Independent variables**

 The **main independent variable**will be the treatment group (gabapentin or placebo).

**Independent variables:**

**-**Socio-demographic variables: age, sex and BMI. (source: interview and collection of anthropometric data at the baseline visit: age, sex, BMI.

- Percentage of adherence to the prescribed treatment: At the final visit, the patient will be invited to bring the bottle with gabapentin medication and a count will be made of the pills he has taken and those that have been prescribed.

- Presence of Diabetes Mellitus, autoimmune diseases and neuropathies.

(sources: interview and clinical history)

-Concomitant medication: analgesics, tricyclic antidepressants, opioids, HZ vaccination, etc. (sources: interview and clinical history).

**7.5. Pilot study**

 A pilot study will be conducted with 6 investigators that will include two patients each, in order to know the degree of acceptance of the protocol by health professionals and patients, checking the adequacy of the circuits in the detection of patients with herpes zoster, offering participation in the study in a period not exceeding 72h, communication with the research unit and subsequent randomization.

**8. ADVERSE EFFECTS**

Incidence of adverse events and severe AA. In a double-blind study in patients with neuropathic pain treated with gabapentin, somnolence, peripheral edema and asthenia appeared in a higher percentage in patients> 65 when compared with younger patients. Apart from these facts, clinical investigations in this age group do not indicate different adverse events from that observed in young patients.

Despite this, as there have not been systematic studies in patients older than 65 years and the trial foresees the inclusion of patients older than 50 years, information regarding these AAs will be systematically collected. (Gabapentin, technical data sheet of the product).

When gabapentin was prescribed, several adverse effects have been detected, such as:

Disorders of blood and lymphatic system:

Common: leukopenia.

Rare: thrombocytopenia.

Immune system disorders:

Rare: allergic reactions (for example, urticaria).

Metabolism and nutrition disorders:

Common: anorexia, increased appetite.

Psychiatric disorders:

Frequent: hostility, confusion and emotional instability, depression, anxiety, nervousness, abnormal thinking.

Rare: hallucinations.

Nervous system disorders:

Very common: drowsiness, dizziness, ataxia.

Common: seizures, hyperkinesia, dysarthria, amnesia, tremor, insomnia, headache, sensations such as paresthesia, hypesthesia, abnormal coordination, nystagmus and increase, decrease or absence of reflexes.

Rare: movement disorders (for example, choreoathetosis, dyskinesia, dystonia).

Eye disorders:

Common: visual disturbances such as amblyopia, diplopia.

Ear and labyrinth disorders:

Common: vertigo.

Rare: tinnitus.

Cardiac disorders:

Rare: palpitations

Vascular disorders:

Common: hypertension, vasodilation.

Respiratory, thoracic and mediastinal disorders:

Common: dyspnea, bronchitis, pharyngitis, cough, rhinitis.

Gastrointestinal disorders:

Common: vomiting, nausea, dental anomalies, gingivitis, diarrhea, abdominal pain, dyspepsia,

constipation, dry mouth or throat, flatulence.

Rare: pancreatitis.

Hepatobiliary disorders:

Rare: hepatitis, jaundice.

Disorders of the skin and subcutaneous tissue:

Common: facial, purple edema most often described as contusions resulting from physical trauma, rash, pruritus, acne.

Rare: Stevens-Johnson syndrome, angioedema, erythema multiforme, alopecia.

Musculoskeletal and connective tissue disorders:

Common: arthralgia, myalgia, back pain, spasms.

Renal and urinary disorders:

Uncommon: incontinence

Rare: acute renal failure.

Disorders of the reproductive system and breast:

Common: impotence.

General disorders and alterations in the place of administration:

Very frequent: fatigue, fever.

Common: peripheral or generalized edema, abnormal gait, asthenia, pain, malaise, flu syndrome.

Rare: reactions due to withdrawal syndrome (mainly anxiety, insomnia, nausea, pain, sweating), chest pain. Unexpected deaths have been reported, in which a causal relationship with treatment with gabapentin has not been established.

Complementary explorations:

Common: decreased white blood cell count, weight gain.

Rare: fluctuations of blood glucose in patients with diabetes, increased liver function tests.

Traumatic injuries and poisonings:

Common: accidental injuries, fracture, abrasion.

 In severe cases, acute pancreatitis and suicidal tendencies have been described during treatment with gabapentin.

Adverse events are classified as:

Mild: The adverse event related to the treatment with gabapentin does not modify the normal life of the patient.
Moderate: The adverse event related to the treatment with gabapentin alters the normal life of the patient (involves medical visit or sick leave) 
Serious: The adverse event related to treatment with gabapentin directly endangers the patient's life. 
Death: The patient is death because of treatment with gabapentin.

Serious adverse events are considered to be any serious or fatal withdrawal symptom and any cause of hospitalization or death, whether or not caused by treatment with gabapentin.

If a serious adverse event occurs, the record of serious adverse events should be filled out (Annex 6) and sent by fax before 48 hours to the coordinating center: [name].

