**20. ANNEX 6**

**NOTICE OF ADVERSE EVENTS**

**NOTIFICATION OF SERIOUS ADVERSE EVENTS**

I. EVENT INFORMATION

1. patient initials

2. date of birth

3. date start event

4. mark all cases related to the adverse event:

              () death

              () hospitalization or prolongation of hospitalization

              () persistent disability

              () threat to life

5. adverse event:

II. DRUG INFORMATION

1. Suspected drug (include generic name):

2. Has it disappeared after interrupting drug administration?

 _______________________________________________________________

3. Daily dose: _______________________

4. Route of administration: __________________

5. Indication of the drug: _________________________________________________________

6. Administration dates: from / / until / /

7. Has the event reappeared after reintroducing the drug?

_______________________________________________________________

III. CONCOMITANT DRUGS

CONCURRENT DRUGS AND ADMINISTRATION DATES

IV. INVESTIGATOR’ NAME, ADDRESS AND TELEPHONE

V. DESCRIPTION OF THE EVENT AND CLINICAL HISTORY

Description of the event and relevant clinic (including laboratory data, diagnostics, allergies, etc.)

DATE OF THE REPORT:

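### The section 8 rule for reporting serious adverse events does not match the criteria on its own Annex 6 form, and all four grades are tied to gabapentin, so events judged unrelated have no grade

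*Protocol*

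**What the plan says.** Section 8 of the protocol does two things in close succession.

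First, it defines four grades. Two of them open as follows: "Mild: The adverse event related to the treatment with gabapentin does not modify the normal life of the patient" and "Moderate: The adverse event related to the treatment with gabapentin alters the normal life of the patient". The Serious line is for an event related to gabapentin that endangers life, and the Death line is for a death caused by gabapentin.

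Second, it defines what must be reported quickly: "Serious adverse events are considered to be any serious or fatal withdrawal symptom and any cause of hospitalization or death", followed by "whether or not caused by treatment with gabapentin". The action follows from that definition: "If a serious adverse event occurs, the record of serious adverse events should be filled out (Annex 6"), to be faxed to the coordinating centre within 48 hours.

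The Annex 6 form asks the investigator to mark which of four criteria apply: death, "hospitalization or prolongation of hospitalization", "persistent disability" and "threat to life".

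Elsewhere, section 7.1 has every adverse event recorded at each follow-up visit with a description, dates and possible causality to the study drug. Section 3.2 sets the safety objective as the percentage of patients who report adverse events. Section 7.3 names the safety variable as the incidence of adverse effects and of severe ones.

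**The concern.** The rule that tells an investigator when to complete the form is narrower than the form. Someone who follows section 8 to the letter would not open Annex 6 for a patient left with a lasting disability, or one who survived a life-threatening event, if that patient was not admitted and the event was not a withdrawal symptom. Patients are recruited and followed in primary care, so an event without admission is not a remote possibility. What is at stake is whether such events reach the Safety Committee promptly. Section 10.1 makes that committee responsible for reviewing serious adverse effects and notifying the medicines agency where necessary.

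The grades raise a second, separate issue. They combine how bad an event was with what caused it. Section 7.1 already records causality as its own item, so the grade need not carry it. As worded, an event judged unrelated fits none of the four categories. Any table of events by grade would then cover only the events that investigators attributed to treatment.

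**Working it through.** No sample size, power or rate enters this point, so the check is a comparison of texts.

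**Step 1. Annex 6 criteria against the section 8 reporting sentence.**

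| Annex 6 criterion | In the section 8 sentence? |
| --- | --- |
| Death | Yes, whatever the cause |
| Hospitalisation or its prolongation | Hospitalisation yes, whatever the cause; prolongation not named |
| Persistent disability | No |
| Threat to life | Not as a general criterion |

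Threat to life does appear in section 8 in two limited ways: in the Serious grade, which covers only events related to gabapentin, and through the inclusion of serious withdrawal symptoms. So of four criteria, one is absent outright and one is only partly covered.

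**Step 2. What the rule does with particular events.** Assume that each event is not a withdrawal symptom.

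| Event | Section 8 grade | Section 8 reporting sentence | Annex 6 box |
| --- | --- | --- | --- |
| Life-threatening, not admitted, survives, judged related | Serious | Not listed | Yes |
| Life-threatening, not admitted, survives, judged unrelated | None | Not listed | Yes |
| Persistently disabling, not admitted, judged unrelated | None | Not listed | Yes |
| Admission, judged unrelated | None | Listed | Yes |
| Death, judged unrelated | None | Listed | Yes |

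The first three rows show the reporting gap. In the first row the event is called Serious by the grade, yet it is not listed in the sentence that defines a serious adverse event. Rows two to five show the grading gap.

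**Step 3. How long an event outside the rule could wait.** Follow-up visits are at weeks 1, 4, 6 and 12. The intervals from week 0 are 1, 4 − 1 = 3, 6 − 4 = 2 and 12 − 6 = 6 weeks. The longest possible wait for entry at a scheduled visit is therefore 6 weeks (6 × 7 = 42 days), against 48 hours (2 days) by the expedited route. The items that section 7.1 lists for each event include neither grade nor seriousness.

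**Step 4. Which safety summaries depend on the grades.**

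- Percentage of patients with adverse events (section 3.2): no condition on relatedness, so not affected.
- Count of serious adverse events as section 8 defines them: expressly regardless of cause, so not affected by the grade wording.
- Severe events (section 7.3): severe is not one of the four grade names. If it means the top grades, it is conditional on attribution to gabapentin. If it means serious adverse events, it follows the section 8 definition, which is narrower than the form. The protocol does not say which is meant.

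**The case against.** The strongest reply is that little would be lost in practice. Every adverse event is recorded in both arms at each follow-up visit. Section 10.2 makes investigators responsible for communicating serious adverse effects. The Serious grade, a few lines above the reporting instruction, mentions danger to life, so a sensible investigator might well complete the form. This stands in part. A reader might infer from the mismatch that serious events would go unrecorded altogether; the documents do not support that, and the gap concerns the expedited route only. The Serious grade does not close that gap. It is limited to related events, it says nothing about disability, and the form is tied to the definition of a serious adverse event, not to the grade.

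A reader might also infer from the grade wording that the two arms are not compared on equal terms, or that events on placebo can never be graded. The documents do not bear this out. The adverse event percentage carries no relatedness condition, and serious events count whatever their cause. No comparison by grade is explicitly planned. Investigators are blinded (section 4.3) and judge causality against the study drug, so an event on placebo can be judged related. Section 12 accepts that side effects may reveal the allocation, which could make attribution differ between arms. The protocol gives no attribution rates, however, so any figure for a resulting bias would be invented. What remains is that events judged unrelated have no grade, and that this matters wherever grades are summarised.

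**Conclusion.** The point holds as two wording defects in section 8. The reporting rule omits persistent disability and covers threat to life only in part, although its own form asks for both. The consequence is a possible loss of expedited reporting for disabling or life-threatening events without admission or death that are not withdrawal symptoms, with a delay of up to six weeks before entry at a scheduled visit. This assumes that investigators apply the section 8 sentence as written.

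All four grade lines are conditional on gabapentin. The effect is confined to summaries by grade, and reaches the section 7.3 safety variable only if severe there means the top grades. The defects do not bias the overall adverse event percentage and do not touch the efficacy analysis. They should still be corrected, since safety is in the title and among the objectives and the correction is simple.

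**What to change.** - In section 8, state the same four seriousness criteria as Annex 6 (death, hospitalisation or its prolongation, persistent disability, threat to life), each regardless of cause, and keep the existing withdrawal-symptom item.
- Remove the gabapentin attribution from all four grade lines. The phrase is not identical throughout: Mild and Moderate share one wording, Serious differs slightly, and Death uses a causal clause. Each must be edited separately, since deleting a single phrase would leave some grades conditional.
- Add the grade to the items recorded for every event in both arms under section 7.1, with causality kept as its own field.
- Say in section 7.3 whether severe means particular grades or serious adverse events, and use the section 8 term.

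The cost is a wording amendment, a note to investigators, one more recorded item per event and slightly more Annex 6 forms. Treatment, visits and sample size do not change.

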**9. ETHICS**

This project has been submitted to the approval of the Ethical Committee of the Balearic Islands. The health professionals participating in the study will sign a document committing themselves to guarantee the confidentiality of the data of all the patients (annex 3, 4). Before initiating any procedure of the study, the informed consent of each patient must be obtained (annex 2). The patient information sheet will contain the necessary information (annex 1) and will be previously approved by CEIC. The consent will be kept with the documents of the investigator’s study. To obtain consent, the recommendations included in the Declaration of Helsinki (annex 5) will be followed and the investigators will sign a confidentiality document of the collected data.

**10. PRACTICAL CONSIDERATIONS**

**Organization of the study and responsibilities**

**10.1. Monitoring Committees**

**A) Executive Committee.**It will be formed by [name] [name], [name] [name], will supervise the quality and methodological rigor of the data collection and analysis. It will also be responsible for developing a mechanism for transmitting information to the investigators of each center. It will evaluate the results of the monitoring and will be responsible for correcting the detected problems. It will also review and approve the presentations or publications made.

**B) Coordination Committee:**[name] [name] and [name]. They will be responsible for the uniform application of the protocol in the different health centers and to maintain the rhythm of inclusion, organize the dispatch and collection of material, coordination of the study staff.

**C) Safety Committee:**Will be formed by [name] [name], [name] [name]; their role will be to receive, review and notify if necessary to the Spanish Agency of Medicines, serious adverse effects of the study. The opening of the randomization code will also be within its functions.

**10.2. Responsibilities**

Each investigators who decides to participate in the study, will be responsible for the recruitment of patients, the request and achievement of written informed consent, the application of the inclusion and exclusion criteria, the notification of inclusion to the coordinating center, the patient’ visit schedule and periodic evaluation according to the study protocol, of the collection and periodic sending of data to the coordinating center and of the communication of serious adverse effects.

The coordinating center of the study will be responsible for the planning of the study, the design and implementation of the data collection instruments, the statistical analysis, the edition of the operations and procedures manual, the organization of the training sessions, standardization and certification of the investigators, to organize the pilot study and its analysis, the subsequent edition of the manual and CRD if necessary, sending of questionnaires and study materials to the participating centers, to supervise and coordinate the collection of data (face-to-face monitoring in a sub-sample) of patients and data processing of all centers.

The general coordination will be in charge of the Research Unit of the Primary Care Department of Mallorca.

**11. STATISTICAL ANALYSIS**

**Global data management**

Every subject included in the study will be assigned a unique numerical identifier created with an algorithm based on the codes of the community of origin, the Health Center to which it belongs, the collaborating doctor and the case number.

The identifier will be present in each of the tables of the study. Here are the different data tables that will be included in the study:

1. Inclusion table. It will correspond to the data of the CRDs of visits -1 & -0.
2. Tracking table. They correspond to the data of the CRDs of visits -1, -2 and -3.
3. Final visit table. They correspond to the data of the CRDs of the visit -4.
4. Monitoring table. Record of the monitoring carried out for each of the included patients.

The ***Teleform***program has a verification module that guarantees the quality of the data entry. Nevertheless, 30% of the questionnaires will be entered manually and the data will be validated by checking the file concordance with the ***Epiinfo***program**.**The data in printed support will be stored locally and copies will be sent periodically to the coordinating center, where they will be processed and stored in magnetic support. Two backup copies will be made on magnetic tape of all the data entered each month. An IBM 3500 backup 400 Gb server appliance will be used.

All statistical analyzes will be carried out with the **SPSS for Windows v15**. The level of statistical significance is established at 5% bilaterally. The statistical analysis will be the responsibility of the Research Unit of the Primary Care Management of Mallorca.

For the statistical analysis, the SPSS program for Windows v.15:

- Descriptive analysis, labeling and filtering of data: evaluation of atypical and extreme values ('outliers´), detection and labeling of lost values and / or non-applicable values, description of the distribution of each of the variables.  Normality tests, scatter plots.

- Baseline comparative analysis: Comparison between sociodemographic characteristics between the intervention group and the control group, through the t-test and chi-square test. In case of non-fulfillment of normality assumptions, non-parametric tests will be applied.

- Final comparative analysis: Comparison of the clinical characteristics, of medication between the groups of placebo and treatment, using t-test and chi-square test. If the normality assumptions are not met, nonparametric tests will be applied. The clinical relevance of the intervention will be determined from the absence of pain at 12 weeks in the control and intervention groups and in the benefit / risk ratio of the intervention, the relative risk reduction (RRR), the absolute risk reduction (ARR) and the number of patients needed to treat will be calculated (NNT). A crude analysis will be performed by chi-square and adjusted by logistic regression of the baseline characteristics that show to be different in the control and intervention groups. All the analyzes will be carried out by intent to treat (`intention to treat '). The level of statistical significance is established at 5% bilaterally.

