Despite the advances made in its treatment and prevention, PHN pain is difficult to control, therefore NPH continues to be a significant clinical problem. At present, several pharmacological strategies are available for the treatment of NPH, but their efficacy is limited, and it is associated with the appearance of adverse effects. This has led to the search for therapeutic alternatives applicable during the acute phase of the infection to prevent its onset.

The results of systematic reviews and clinicals trials indicate that the use of systemic antivirals during the first 72 h after the appearance of the rash accelerate healing and decrease the duration of pain; they also shorten the duration of PHN, but its effect on its incidence It is not well established (3,10). In this same line, the use of systemic corticosteroids in the acute phase has also been proposed as an alternative to prevent PHN but has only been shown to be effective in pain control and quality of life. Corticosteroids have been associated with a reduction in the incidence of PHN, but its use is controversial (3.5).

Currently the efficacy and safety of the new varicella- zoster vaccine has been evaluated in the Shingles Prevention Study, a randomized, multicenter, double-blind, placebo-controlled study that included more than 38,000 immunocompetent individuals of 60 or more years, with no history of HZ, with a mean follow-up of more than 3 years. The use of the vaccine was associated with a moderate reduction in the burden of the disease due to HZ (61.1%; p <0.001), as well as the incidence of PHN (66.5%, p <0.001). If the patient had developed HZ, the reduction in NPH was 12.46% versus 8.56%, a reduction of 31%. Currently the vaccine is approved for the prevention of HZ and NPH in adults 60 years old and older and more recently, with data only from immunogenicity, has also been approved for adults 50-59 years. Nevertheless, it is not known if the vaccine protection lasts beyond 4 years or if a revaccination is necessary. The use of vaccine use is currently not generalized (5,12).

On the other hand, given that intense pain during the acute phase of HZ is a known risk factor for the subsequent development of PHN, another feasible therapeutic strategy would be based on the reduction of the incidence of PHN once the HZ appeared by optimal pain control in this phase.

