**5.2. Sample size**

The sample size has been calculated according to the main efficacy variable. The percentage incidence of PHN in patients in the valaciclovir + placebo group is expected to be at least 45% (Helgason S, Petursson G, Gudmundsson S, Sigurdsson JA. Prevalence of postherpetic neuralgia after a first episode of herpes zoster: prospective study with long term follow up BMJ 2000 Sep 30; 321 (7264): 794-6.) and in the valaciclovir + gabapentin group of 20.3% ( Lapolla W, Digiorgio C, Haitz K, Magel G, Mendoza N, et al. incidence of postherpetic neuralgia after combination treatment with gabapentin and valacyclovir in patients with herpes zoster: open-label study Arch Dermatol 2011; 147 (8): 901-7 ), We have calculated a follow-up loss rate of 20%; an alpha risk of 5% and a beta risk of 20%. Therefore, it is necessary to recruit 134 patients (67 subjects in each treatment arm).

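### The adjusted analysis of PHN picks its covariates by observed baseline imbalance, so age and baseline pain would usually be left out, and neither the crude nor the adjusted result is named as primary

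*Protocol*

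**What the plan says.** Protocol Section 11 (Statistical analysis) has three relevant parts.

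- **Baseline comparison:** "Comparison between sociodemographic characteristics between the intervention group and the control group, through the t-test and chi-square test". Only sociodemographic characteristics are listed. Section 7.4 gives these as age, sex and BMI, and does not list baseline pain among the independent variables.
- **Final comparison, crude:** "A crude analysis will be performed by chi-square".
- **Final comparison, adjusted:** "adjusted by logistic regression of the baseline characteristics that show to be different in the control and intervention groups". There is no covariate list and no threshold for calling a characteristic different. Nothing states whether the crude or the adjusted result is the primary one.

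Elsewhere the protocol identifies its own predictors. Section 3.1 reports PHN in 36% of zoster patients over 60 and 50% of those over 70, and states that "intense pain during the acute phase of HZ is a known risk factor for the subsequent development of PHN". Section 7.1 records age and VAS at the baseline visit. Section 4.2 randomises in blocks of 6, with no stratification by age or pain stated.

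**The concern.** This is a rule that the protocol states, not a detail left to a later analysis plan; a plan that followed it would inherit it. The rule selects on the wrong criterion. In a randomised trial, differences between arms at baseline arise by chance. A covariate earns its place because it predicts the outcome, and an observed imbalance does not show that. A strong predictor that happens to be balanced is dropped, and an irrelevant variable that happens to be imbalanced is kept.

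Two things are at stake. One is precision that the trial could have from data it already collects. The other is that the adjusted model is not known until the arms have been compared, while two results will be available and neither has been given precedence. The two are also not the same quantity: the adjusted odds ratio is conditional on its covariates and changes with them, whereas the crude comparison is marginal.

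Section 12 adds a reason to want age in the model every time, since it anticipates that losses may fall more on older patients.

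**Working it through.** **1. The planned sample size.** Inputs from Section 5.2: control PHN rate 45% (the text says it "is expected to be at least 45" per cent), gabapentin 20.3%, loss 20%, and "an alpha risk of 5% and a beta risk of 20" per cent. Section 11 makes the test two-sided.

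Unadjusted two-proportion formula with unpooled variance:

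n = (1.96 + 0.8416)² × (0.45×0.55 + 0.203×0.797) / 0.247² = 7.849 × 0.4093 / 0.0610 = 52.7, so 53 per arm.

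53 / (1 − 0.20) = 66.25, so 67 per arm and 134 in total. This matches the protocol exactly. With a pooled-variance calculation, power at 53 evaluable per arm is 78%. The trial was therefore sized for an unadjusted comparison at about 80% power.

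**2. How often the rule lets the predictors in.** Assume that different means p<0.05 and that age and baseline VAS are independent and both screened.

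- Neither enters: 0.95² = 90.25%.
- Exactly one enters: 2 × 0.05 × 0.95 = 9.5%.
- Both enter: 0.05² = 0.25%.

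If 7 to 10 independent characteristics are screened (also an assumption), the chance that at least one is selected is 1 − 0.95⁷ = 30% to 1 − 0.95¹⁰ = 40%. On the literal list in the baseline comparison, VAS is not screened and might never enter.

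**3. Effect on power and type I error.** Simulation with 53 evaluable per arm and 4,000 trials per row. Age and baseline pain are two independent standardised covariates with the same odds ratio (OR) per SD. Intercepts are set so that the overall PHN rates remain 45% and 20.3% in every row. The prognostic odds ratios are assumptions.

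| OR per SD, each | Power: crude chi-square | Power: protocol's rule | Power: both covariates fixed | Fixed minus rule |
| --- | --- | --- | --- | --- |
| 1.0 | 78.7% | 77.8% | 77.6% | −0.2 |
| 1.5 | 79.5% | 78.8% | 80.5% | +1.7 |
| 2.0 | 78.4% | 78.2% | 82.8% | +4.6 |
| 2.5 | 78.8% | 79.2% | 86.4% | +7.2 |

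The Monte Carlo standard error is √(0.8×0.2/4000) = 0.6 points. Type I error across the four rows was 4.1 to 5.0% (crude), 3.8 to 4.3% (protocol's rule) and 4.8 to 5.2% (fixed). The rule performs like the crude test because in about nine trials out of ten it adjusts for neither covariate.

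**4. SF-12, a side point.** With an assumed standardised difference of 0.5, 53 per arm and a baseline correlation r = 0.5, the variance relative to the final score is 1 − r² = 0.75 for ANCOVA and 2(1 − r) = 1.0 for a change score. Power is 73% for a t-test on the final score, 73% on the change score and 84% for ANCOVA. At r = 0.3 and 0.7, ANCOVA gives 77% and 95%.

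**The case against.** The strongest reply is that nothing the trial was planned on is damaged. The crude chi-square is named first, the sample size matches an unadjusted comparison, and that test keeps its planned power. All of this stands. The gain from fixed covariates rests on prognostic strengths that the documents do not give. The two eligible age bands in Section 3.1 overlap, the 1.3% quoted there concerns patients under 50, whom the trial excludes, and baseline VAS is truncated at 4 or above by the inclusion criteria. If the covariates predict nothing, the gain is zero.

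Four stronger readings are tempting, and the documents support none of them.

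- **Inflated false-positive rate.** A reader might infer that data-driven selection raises type I error. In the simulation it does not.
- **Lost planned power.** A reader might infer that the trial is underpowered. A simulation with strong covariates and a conditional log-odds ratio of −1.3 does put crude power near 72%, but it implies a gabapentin PHN rate of about 22.3%, a smaller effect than Section 5.2 assumes.
- **Unblinded selection.** Section 4.3 keeps the statistician blind, and arms can be compared under coded labels. The selection is data-driven, but nothing says it is unblinded.
- **Continuous outcomes ignore baseline.** Section 11 names only a t-test or a nonparametric test, without saying whether final or change scores are compared. However, Section 3.2 frames SF-12 as improvement, the VAS responder outcome is relative to baseline, and MOS-Sleep has no baseline value to use.

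What the reply does not answer is the selection criterion itself and the missing statement of which analysis is primary.

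**Conclusion.** The point holds as one of efficiency and transparency. As written, the adjusted analysis would usually omit the two predictors that the protocol names and collects, and its content depends on chance imbalance. The cost is a forgone gain of about 0 to 7 points of power, an adjusted model that is not fixed before the data are seen, and an undecided choice between two results. The validity of the crude test, the type I error and the sample size are unaffected. The figures assume a p<0.05 threshold, two independent covariates with odds ratios per SD between 1.0 and 2.5, 53 evaluable patients per arm, and the protocol's own PHN rates.

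**What to change.** In Section 11, final comparative analysis:

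1. Remove the condition that limits adjustment to characteristics found to differ between the arms. State that the logistic regression of PHN at week 12 includes treatment, age and baseline VAS, whatever the baseline comparison shows.
2. State, before any comparison of the arms, whether the crude or the adjusted analysis is primary. The adjusted model is more efficient if the covariates are prognostic; if they are not, the simulated loss against the crude test is about 1 point (77.6% against 78.7%). Keeping the crude test as primary stays closest to the sample-size calculation.
3. Because the adjusted odds ratio is conditional, take ARR and NNT from the crude proportions or by standardisation from the model.
4. Optionally, analyse SF-12 by ANCOVA on its baseline value.

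The cost is wording. Age, VAS and SF-12 are already recorded at baseline, and 134 patients remain sufficient under the protocol's assumptions.
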